### Study Population

The study aims to enroll all Flemish GPs who are affiliated to a *“GP circle” (ie, huisartsenkring or HAK)*. The *HAK* is the local focal point for GPs and policy makers to implement health policy in primary care, and provides continuous medical education [23]. HAKs are subsidized by the Flemish government and are organized by geographical zones. In 2016, 8163 GPs were active in Flanders [24]. Among them, 6211 (76.1%) are affiliated to one of the 86 HAKs (Zorg en Gezondheid, personal communication via email, September 2016). The choice of enrolling only GPs affiliated to a HAK is a pragmatic one: GPs can be easily accessed through HAKs, and the geographical aspect provides an opportunity for nonindividual comparison. No data are available to describe GPs who are not affiliated to HAKs, but they are assumed to be mainly working in nonprimary care contexts such as specialist centers for educational health care (Zorg en Gezondheid, personal communication via email, September 2016).

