#### Randomization Strategy

Intervention groups are identifiable in HIV-surveillance data using the administrative code referring to geographical zones defined by the National Institute of Statistics (ie, NIS code). HAKs that correspond to the same NIS code have been merged, regrouping 86 HAKs into 76 clusters. Each cluster is randomly allocated by the study team to one of the three intervention conditions using block sampling. Block sampling took the variability of the different target populations at risk for HIV in the intervention groups into consideration: each block consists of three clusters with approximately the same number of SAMs in the respective NIS-code areas. The main reason for this approach is that the intervention is assumed to generate the largest effect among SAMs, given their low testing rates in primary care. Since SAMs are unevenly distributed over Flanders with the largest communities living in central cities [29], block randomization assures that the expected effect is equally distributed across the three intervention levels. This approach results in 25 clusters being assigned to intervention level 1 or 2, and 26 clusters assigned to the control condition.

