#### Data Extraction and Management

For outcome evaluation, HIV-surveillance data will be transferred through technical interfaces with encrypted data to Sciensano by Healthdata, the agency responsible for data captation and secure data transfer. Data will be checked and duplicated records will be removed. Sciensano will provide the aggregated data of both HIV tests and HIV diagnoses to the researchers for further analysis.

For process evaluation, data from the online survey are collected anonymously and extracted through a downloadable Excel Database. Interview recordings will be transcribed verbatim. Pseudonymized data are managed and archived by the Institute of Tropical Medicine in locked and secured (digital) locations that are only accessible by the researchers.

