#### Data Analysis and Statistical Methods

Using the stepped-wedge design, the distribution of results across unexposed observation periods is compared with that across the exposed observation periods. To determine the intervention’s effectiveness, primary and secondary outcomes at the three levels are compared against each other at three different time periods, that is, baseline and before March 2017, from March to August 2017, and from August 2017 to December 2018 (data available in late 2019).

Poisson regression is used to estimate the relative change in outcome variables. This change is explored through several alternative models, comparing the intervention group to the control group or to each other over time. In addition, we are investigating the differences in the ability to diagnose groups that are at high risk for acquiring HIV (MSM, SAMs, people who inject drugs, and others) and timely diagnosis (represented by CD4-cell count in three categories: less than 200 cells/mm^3^, 200-350 cells/mm^3^, and above 350 cells/mm^3^) across time periods and interventions.

To quantify the level of uncertainty associated with the estimates, Poisson regression models will be fitted to the data using Bayesian modeling under weakly informative priors. For each parameter, we will report the 90% central credible interval from the marginal posterior distribution.

Within the process evaluation, survey data are analyzed descriptively to compare groups with different intervention exposures in terms of self-perceived effects of the intervention levels such as gains in knowledge, self-efficacy to test, and future intention to use the intervention tools.

Qualitative data collected through telephone interviews are analyzed inductively. Using NVivo 8 (QSR International), a data-driven codebook will be established according to the principles of thematic analysis [31].

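### 76 clusters are randomised, but the only uncertainty model named is Poisson regression with no stated cluster or overdispersion term; if fitted as written, 90% intervals are far too narrow for HIV-test counts when cluster rates drift, and mildly to moderately so for diagnoses

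*Protocol article*

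**What the plan says.** Protocol article, Randomization Strategy: "HAKs that correspond to the same NIS code have been merged, regrouping 86 HAKs into 76 clusters". Then: "Each cluster is randomly allocated by the study team to one of the three intervention conditions using block sampling". The split is "25 clusters being assigned to intervention level 1 or 2, and 26 clusters assigned to the control condition", that is 25 + 25 + 26 = 76. The same section concedes that "SAMs are unevenly distributed over Flanders with the largest communities living in central cities".

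Protocol article, Data Analysis and Statistical Methods: "Poisson regression is used to estimate the relative change in outcome variables". Several alternative models are foreseen, but they are described only by which groups are compared. On precision the section says: "To quantify the level of uncertainty associated with the estimates, Poisson regression models will be fitted to the data using Bayesian modeling". It adds weakly informative priors and a 90% central credible interval for each parameter. The three conditions are compared over three periods: before March 2017, March to August 2017, and August 2017 to December 2018.

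On data, Data Collection says that test counts are aggregated by cluster and intervention level and that each diagnosis is linked to a cluster number. Informed Consent mentions grouping diagnoses by GP circle and analysing every two months. Data Extraction and Management says: "Sciensano will provide the aggregated data of both HIV tests and HIV diagnoses to the researchers for further analysis".

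**The concern.** A Poisson likelihood sets the variance of each count equal to its mean. If nothing is added, counts from the same cluster are treated as independent given the arm and period terms, and a cluster's rate may not move over time except through those terms. Because whole clusters are allocated, any local movement (a new practice, a local campaign, uneven uptake of PrEP) falls entirely on one arm and belongs in the error of the arm comparison. Weakly informative priors on the regression coefficients do not supply that variance.

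The consequence grows with the size of the count. Test counts are large, so their pure Poisson error is very small and modest local drift swamps it. A chance difference between arms in GP testing could then carry a narrow interval and read as an effect, in a study meant to inform official testing guidelines (Abstract, Conclusions). Diagnosis counts per cluster are small, so Poisson error dominates and the damage is much less.

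**Working it through.** **No plan figure to reproduce.** The article gives no sample size, power, intracluster correlation, between-cluster CV or count per cluster. All volumes and CVs below are assumptions.

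**Formula.** Let μ be the mean count per cluster and period, and k the CV of the cluster-by-period rates. With clusters of equal size, the variance of an arm-by-period (pre/post) log rate ratio is inflated over the Poisson variance by

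VIF = 1 + μk²,

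and a nominal 90% interval covers with probability 2Φ(1.645/√VIF) − 1. Poisson likelihood intervals stand in for credible intervals under weak priors.

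**Assumed volumes.** For a baseline of 14 months (January 2016 to February 2017) and a last period of 16 months, 5,000 tests a month gives 5,000 × 14/76 = 921 and 5,000 × 16/76 = 1,053 per cluster, so μ is about 1,000. For 15 to 25 diagnoses a month, μ runs from 15 × 14/76 = 2.8 to 25 × 16/76 = 5.3. The Introduction's national 1.25 diagnoses per 1,000 tests is 800 tests per diagnosis. If that ratio held for GPs, 15 diagnoses a month would go with 15 × 800 = 12,000 tests, so 5,000 is not a high assumption.

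**Baseline-adjusted contrast, equal clusters (analytic).**

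| Outcome | μ | k | VIF | SE ratio | Coverage |
|---|---|---|---|---|---|
| Tests | 1,000 | 0.05 | 3.5 | 1.9 | 62% |
| Tests | 1,000 | 0.10 | 11 | 3.3 | 38% |
| Tests | 2,000 | 0.05 | 6 | 2.4 | 50% |
| Tests | 2,000 | 0.10 | 21 | 4.6 | 28% |
| Diagnoses | 2 | 0.10 | 1.02 | 1.01 | 90% |
| Diagnoses | 2 | 0.20 | 1.08 | 1.04 | 89% |
| Diagnoses | 4 | 0.10 | 1.04 | 1.02 | 89% |
| Diagnoses | 4 | 0.20 | 1.16 | 1.08 | 87% |

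With k = 0, VIF = 1 and coverage stays at 90% for both outcomes, however much the clusters differ in level. A gamma-Poisson simulation of 25 against 26 clusters agreed.

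**Uneven cluster sizes (simulated).** Blocks of three, level 2 against control, no true effect, 14 months before and 16 after:

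| Outcome | k | Equal sizes | Lognormal sizes, sigma 1.2 |
|---|---|---|---|
| Tests, 5,000/month | 0.05 | 64% | 43% |
| Tests, 5,000/month | 0.10 | 41% | 25% |
| Diagnoses, 15-25/month | 0.10 | 88-89% | 87-88% |
| Diagnoses, 15-25/month | 0.20 | 86-88% | 80-84% |

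The two columns fit together. If s is the CV of cluster size, VIF = 1 + μk²(1 + s²). The simulated SE ratio for tests at k = 0.05 with sigma 1.2 was 3.0, so 9 = 1 + 2.5(1 + s²) and 1 + s² = 3.2. For diagnoses at μ = 4 and k = 0.20, VIF = 1 + 0.16 × 3.2 = 1.51, SE ratio 1.23 and coverage 82%, inside the simulated 80-84%.

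**Contrast that ignores baseline.** Stable differences between clusters now count. With a between-cluster CV of 0.5 and equal expected sizes, VIF = 1 + 0.25μ. For diagnoses, μ = 2 gives 1.5 (SE ratio 1.22, coverage 82%) and μ = 4 gives 2.0 (1.41, 75%). For tests, μ = 1,000 gives 251 (about 16, 8%).

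**The case against.** The strongest reply is that silence is not a statement. A reader might infer that the protocol commits to a Poisson model with independent counts and rules out random effects. It does not: a hierarchical Poisson model fits the same words, and an article commonly leaves such terms to a fuller document. That stands, and it is why the point is conditional. What remains is that the paragraph devoted to uncertainty fixes the likelihood, the fitting method, the class of prior and the interval level. The alternative models it mentions differ in the groups compared, not in variance structure. Followed as written, the analysis omits the variation that cluster allocation brings in.

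Three other stronger readings also fail.

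- **Uneven clusters alone make the intervals too narrow.** Stable differences cancel in a contrast that uses each arm's own baseline, and the plan compares periods that include baseline. Drift is needed; uneven sizes only amplify it.
- **The primary outcome is badly affected.** At CV 10% the loss is at most about three percentage points. Lower values at CV 20% depend on an assumed strong spread of cluster sizes: 80-84% with sigma 1.2, against 86% with sigma 0.6 and 86-88% with equal sizes.
- **The researchers will receive only arm totals.** Aggregated does not mean that. Data Collection and Informed Consent already foresee cluster or GP-circle counts and two-month bins.

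For tests, the result also depends on drift not being tiny: at CV 1% and 2% with sigma 1.2, coverage is 85% and 74%. The Discussion names possible sources of drift (PrEP from June 2017, other testing initiatives), but whether they differ by cluster is an assumption. Finally, the article states no decision threshold, so the harm is to the reading of intervals, not to a formal test.

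**Conclusion.** The point holds in conditional form: the named uncertainty model does not match the unit of randomisation, and fitted as written it understates uncertainty whenever cluster rates drift differently. The effect is large for GP-prescribed tests, a secondary outcome: roughly 40-65% coverage at a cluster-by-period CV of 5% and 25-40% at 10%. It is small to moderate for the primary outcome in the baseline-adjusted contrast, and nil without drift. It becomes material for diagnoses (about 75-82%) if arms are compared without their own baseline, which the open list of alternative models does not exclude. The direction follows from the model; the sizes rest on the assumed volumes, CVs and cluster-size spread and cannot be fixed from the article.

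**What to change.** State that the Bayesian Poisson models are fitted to cluster-by-period counts with a cluster random intercept and a cluster-by-period random effect, or a negative binomial equivalent, for the primary outcome and every count outcome. No new data request is needed beyond confirming that the aggregated file passed to the researchers keeps the cluster identifier and the time bin. The modelling cost is two variance terms in an analysis that is already Bayesian. The price is wider intervals: at the assumed drift of 5-10%, about 2 to 5 times wider for tests with equal-sized clusters (more if sizes are very uneven), and little change for diagnoses in the baseline-adjusted contrast.

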### Availability of Data and Materials

Datasets used and/or analyzed during the study are available from the corresponding author on request.

### Ethics and Dissemination

#### Informed Consent

Strict attention to maintain confidentiality is paid at every stage of data collection, analysis, and storage. Data extraction measures will be put in place to ensure that individual HIV patients cannot be identified (grouping of diagnosis as per HAK, analysis every 2 months). HIV-testing and diagnosis data will be managed through the legal entities in charge of the HIV/AIDS surveillance system (Royal Decree of October 8, 1996) authorized by the Belgian Privacy Commission.

To ensure transparency, GPs receive the HIV-testing advice, with an accompanying email that explains that the dissemination of the advice is part of the study monitoring the intervention’s effects through routine data collection. During the training sessions, GPs are informed of the same. The structured questionnaire for GPs contains an introductory statement with information stating that filling in the questionnaire is considered as providing informed consent.

Oral informed consent is obtained before the telephone interview from the participants, who agree to interviewed, in addition to their permission to audio-record the interview.

#### Dissemination

Results of the study will be disseminated at scientific conferences targeting GPs and HIV experts and through articles in GP-specific media and international peer-reviewed journals.

#### Ethical Approval

This study has been approved by the Institutional Review Board of the Institute of Tropical Medicine, Antwerp (approval number: 1228/18; dated January 6, 2017). The study is carried out according to the principles stated in the Declaration of Helsinki and according to established international scientific standards.

#### Consent to Participate

Not applicable for study effectiveness: analysis of HIV-testing and HIV-diagnosis data is managed through the legal entities in charge of the HIV/AIDS surveillance system (Royal Decree of October 8, 1996), authorized by the Belgian Privacy Commission. For transparency, GPs receive an accompanying email together with the HIV-testing advice, which explains that the dissemination of the advice is part of the study monitoring the intervention’s effects through routine data collection. During the training sessions, GPs are informed of the same.

With regard to the evaluation of the study’s feasibility, acceptability, and GPs’ fidelity to the advice, the structured questionnaire for GPs participating in the evaluation contains an introductory statement with information stating that filling in the questionnaire is considered as providing informed consent. Similarly, oral informed consent is obtained before the telephone interview from the participants, who agree to be interviewed, as well as their permission to audio-record the interview.

## Results

The study was funded in 2016 and was ethically approved in January 2017 (see Multimedia Appendix 1). The intervention implementation started in January 2017 and ended in December 2018. Data was completed in October 2019 and was the starting point for the ongoing data analysis. The results are expected to be published in the second half of 2020. The intervention study described in this protocol has been funded through the framework of the European HIV-ERA JTC 2014 (see Multimedia Appendix 2) and the Belgian Funding Agency IWT 140922. The Institute of Tropical Medicine is the study sponsor.

## Discussion

This study will deliver useful information on the implementation and effectiveness of an intervention to promote HIV testing among GPs in Flanders. The participatory intervention development strategy allows for a high degree of tailoring of the intervention to the needs of primary care providers. This should lead to a sustainable intervention [32] with high intervention effectiveness [33]. Systematically collected experiences on disseminating and adopting the HIV-testing advice can inform further development of national HIV-testing policies, sexual health strategies, and GPs’ respective roles in these. Yet, this approach of a real-life intervention trial has its limitations: spill-over effects among intervention levels may occur, as GPs not included in the respective intervention condition may download the advice from the GP umbrella organization’s website or may attend training events of a neighboring HAK. The influence of other initiatives to promote HIV testing cannot be excluded, for example, media messages on HIV testing or HIV prevention. Information on the background of GPs not affiliated to a GP circle is lacking and may cause a selection bias.

The use of surveillance data for analysis, however, provides an opportunity to evaluate a real-life intervention including all Flemish GPs. The formative research indicated this as the most feasible data collection method, enabling long-term follow-up while not overburdening busy GPs. However, such routine data are only collected once a year, therefore causing a delay in data access. Detailed information on specific HIV-testing conditions in primary care practices and profiles of testers cannot be collected. Privacy issues impede further subanalyses (eg, sociodemographic characteristics of GPs associated with diagnosis of HIV). In addition, other interventions, such as the introduction of preexposure prophylaxis (PrEP) on a national scale in June 2017 might cause changes in the demand for HIV testing and subsequently in the number of HIV diagnoses, making comparisons over time difficult.

This study provides a valuable contribution to evidence-based HIV testing in primary care, since only few interventions for the promotion of HIV testing in primary care have been described in the literature [11,34,35]. These settings may play a greater role in HIV prevention and care continuum [10] in the future with outlined directions in provider-level education interventions [35]. The study’s strong qualitative component will provide practice-based lessons on real-life experiences with HIV testing in primary care and insights into the mechanisms by which the intervention works. This will contribute to a nuanced interpretation of the results of outcome evaluation.

## Appendix

Multimedia Appendix 1 Approval letter Institutional Review Board of the Institute of Tropical Medicine.

Multimedia Appendix 2 Approval European framework HIV-ERA JTC 2014.

Multimedia Appendix 3 Previous peer-review report from the Institute of Tropical Medicine.

## Abbreviations

AB: advisory board
GP: general practitioner
HAK: HuisArtsenKring (GP-circle, local focal point for GPs)
HERMETIC: HIV European Research on Mathematical Modeling and Experimentation of HIV Testing in Hidden Communities
MSM: men who have sex with men
NIS: National Institute of Statistics
RIZIV: Rijksinstituut voor Ziekte en Invaliditeitsverzekering (Belgian National Institute for Sickness and Invalidity Insurance)
SAMs: sub-Saharan African migrants
